### **3.4.3.3 Total Body Height**

At the 24-months-corrected-age visit, the length measurement (lying) will be replaced by height measurement (standing). The body height will be measured in accordance with hospital routine for children of this age.

### **3.4.3.4 Head Circumference**

During the treatment period, the circumference of the patient's head (mm) will be measured, using a nonstretch measuring tape provided for this study, and recorded in the eCRF. Preferably and where possible the same equipment should also be used for assessments made after the treatment period. The measuring of head circumference should be made according to separate detailed instructions. This measurement should be made at Baseline (Day 1), Days 8, 15, 22, and 29, at discharge, and at each scheduled follow-up visit ([Table 6–1](#) and [Table 6–2](#)). Measurements up to discharge should be taken as near to the same time each day as is possible.

### **3.4.3.5 Time to Readiness for Discharge**

The following should be recorded in the eCRF:

- The date when the infant is able to suckle feed (coordinate swallowing and breathing).
- The date when the patient is able to control the body temperature, ie, able to maintain normal body temperature while clothed in an open bed with normal ambient temperature.
- The date when the patient is able to maintain stable cardiorespiratory function.

### **3.4.3.6 Docosahexaenoic Acid (DHA) and Arachidonic Acid (AA)**

Fatty acids, including DHA and AA, will be determined in either serum or plasma at Baseline (Day 1) and at the end of treatment (Day 29). Fatty acids other than DHA and AA are considered exploratory assessments.

Total fatty acids require a blood volume of 200 µL, while 500 µL of blood is required for a complete analysis in both phospholipid and triglyceride fractions. [Section 3.4.7](#) provides further details of the sampling.

### **3.4.3.7 Bayley Scales of Infant and Toddler Development**

A description of the Bayley-III assessment is provided in [Section 3.4.4.6](#).

### **3.4.3.8 Child Behavior Checklist**

The CBCL for 1.5 to 5 years of age is a parent-rated scale that will be used to evaluate mental health and behavioral development of children at 24 months corrected age. It consists of 99 problem items and one open-ended item for recording other problems not listed on the form. Each item will be rated by the parent/primary caregiver on a 0-2 point scale, where 0=not true, 1= somewhat or sometimes true and 2=very true or often true. Instructions on how to complete the CBCL will be given by a trained health care professional and the questionnaire should be completed at the site. For administrative reasons it is allowed to administer the CBCL on a different day than the main visit, as long as the administration takes place within the visit window specified in the schedule of events as shown in [Table 6–2](#).

There are 7 syndrome subscales (emotionally reactive, anxious/depressed, somatic complaints, withdrawn, sleep problems, attention problems and aggressive behavior). These subscales are evaluated by summarizing the ratings for the items comprising each syndrome ([Rescorla 2005](#)). The subscales are also summarized as internalizing problems (emotionally reactive, anxious/depressed, somatic complaints and withdrawn items) and externalizing problems (attention problems and aggressive behavior items), and a total problem score is calculated.

The CBCL is part of the Achenbach System of Empirically Based Assessment (ASEBA) which has been used in several countries in research and clinical work ([Rescorla 2005](#)). The scale has good psychometric properties and confirmation of the reliability and validity of the problem scales have been confirmed for the Dutch version of the CBCL ([Potijk et al 2012](#)).

### **3.4.3.9 Neurodevelopment Disability Composite**

The neurodevelopment disability composite will be assessed at 24 months corrected age and is defined as presence of any one of the following:

- A composite score of less than 85 on any of the cognitive, language or motor domains of Bayley-III
- Bilateral deafness, defined as need for bilateral amplification
- Bilateral blindness, defined as corrected visual acuity of less than 20/200 (or equivalent) in the better eye
- Cerebral palsy (CP), defined as hypotonia, spastic diplegia, hemiplegia or quadriplegia causing functional deficits that require rehabilitation services

Similar neurodevelopment disability composites have been widely used to study neurodevelopmental outcome ([Schmidt et al 2007](#); [Wadhawan et al 2009](#); [Wickremasinghe et al 2012](#)).

## **3.4.4 Safety Assessments**

### **3.4.4.1 Adverse Events**

#### **3.4.4.1.1 Definitions**

##### **Adverse Event**

An AE is defined as any untoward medical occurrence, including a clinically significant laboratory finding, symptom, or disease, in a patient enrolled into this study regardless of its causal relationship to study drug.

##### **Treatment-Emergent Adverse Event**

A treatment-emergent AE is defined as any event not present before exposure to study drug or any event already present that worsens in either intensity or frequency after exposure to study drug.

### Serious Adverse Event

An SAE is defined as any event that

- results in death,
- is immediately life threatening (includes events that put patients at risk of death at the time of the event but not events that may have caused patient death if more severe),
- requires inpatient hospitalization or prolongation of existing hospitalization,
- results in persistent or significant disability or incapacity,
- is a congenital anomaly or birth defect.

Important medical events that may not result in death, be life threatening, or require hospitalization may be considered an SAE when, based upon appropriate medical judgment, they may jeopardize the patient and may require medical or surgical intervention to prevent one of the outcomes listed in this definition.

However, preplanned/administrative hospitalization will **not be considered** as an SAE, for example:

- Hospitalization for a procedure that is planned prior to signing the informed consent for enrolling in the study, without a worsening of a pre-existing disease. The procedure must be documented in the source documents and in the eCRF.
- Hospitalization or prolongation of hospitalization for administrative reasons such as technical, practical, or social reasons, in absence of an AE (eg, preplanned hospitalization for vaccinations according to a vaccination program or hospital general policies). This must also be documented in the source documents and in the eCRF.

Please note that hospitalization or prolonged hospitalization for a complication to the preplanned/administrative procedure remains a reportable SAE.

### **Serious Adverse Drug Reaction**

A serious ADR is defined as any event that fulfills the criteria for an SAE and where a causal relationship between the event and the study drug is suspected by the investigator.

#### **3.4.4.1.2 Eliciting and Documenting Adverse Events**

The investigator is responsible for reporting all AEs that are observed or reported during the study, regardless of their relationship to study drug or their clinical significance.

The investigator will report and monitor AEs of special interest, ie, infections, necrotizing enterocolitis, sepsis, intraventricular hemorrhage, retinopathy of prematurity, hearing impairment, bronchopulmonary dysplasia, and cholestasis. These AEs will be handled as AEs, or if meeting the serious criteria, as SAEs. The AEs of special interest will be discussed in a separate section of the study report.

**Adverse events:** AEs will be recorded from start of treatment on Day 1 until the 3-month follow-up visit.

Adverse events present at the 3-month visit should be followed up at the patient's next visit (6-month [if applicable] or 12 months). Adverse events that have not resolved or stabilized at the 12-months-corrected-age visit should be followed up until satisfactory resolution or until the principal investigator or subinvestigator deems the event to be chronic or not clinically significant or the patient's condition to be stable, but without further recordings in the eCRF.

**Serious AEs:** SAEs will be reported from the time the informed consent has been signed up to the 12-months-corrected-age visit. The investigator will ask the patient's legally acceptable representative about any ongoing or previous (since last visit) events that fulfill the SAE criteria.

Any SAEs present at the 12-months-corrected-age visit should be followed up until satisfactory resolution or until the principal investigator or subinvestigator deems the event to be chronic or not clinically significant or the patient's condition to be stable, but without further recordings in the eCRF. Additional information received regarding patients with ongoing SAEs after 12 months should be reported via fax notification as described in [Section 3.4.4.1.3](#).

**Serious ADRs:** Serious ADRs will be reported up to the 24-months-corrected-age visit. At the time of consent to the follow-up assessments (if not done at the 12-months-corrected-age visit), at telephone contacts and at the 24-months-corrected-age visit, the patient's legally acceptable representative will be asked about any ongoing or previous (since last contact or visit) events that fulfills the SAE criteria. The investigator will then judge if a causal relationship between the SAE and the study drug is suspected i.e., if the SAE is a serious ADR.

Any serious ADRs present at the 24-months-corrected-age visit should be followed up until satisfactory resolution or until the principal investigator or subinvestigator deems the event to be chronic or not clinically significant or the patient's condition to be stable, but without further recordings in the eCRF. Additional information received regarding patients with ongoing serious ADRs after 24 months should be reported via fax notification as described in [Section 3.4.4.1.3](#).

In addition, AEs will be recorded on the eCRF from any study-specific data collected during the study (eg, laboratory values, physical examination findings, ECG changes) or any other documents or data that are relevant to patient safety.

#### **3.4.4.1.3 Reporting Adverse Events**

AEs reported or observed will be recorded on the AE page of the eCRF as described in the eCRF completion guidelines. Information collected will include date and time of onset, investigator-specified assessment of severity and relationship to study drug, date and time of resolution of the event, seriousness, as well as any required treatment or evaluations, and outcome. Adverse events resulting from concurrent illnesses, reactions to concurrent illnesses, reactions to concurrent medications, or progression of disease states must also be reported. All AEs will be followed to adequate resolution. The Medical Dictionary for Regulatory Activities (MedDRA) will be used to code all AEs ([Section 4.10](#)).

Any medical condition that is present at the time that the patient is screened but does not deteriorate should not be reported as an AE. However, if it deteriorates at any time during the study, it should be recorded as an AE.

A hospitalization for administrative reasons in the absence of an AE is not considered to be an SAE. If a patient is hospitalized for a procedure that was planned prior to when the

informed consent was obtained, it is not considered an SAE. For further information, see [Section 3.4.4.1.1](#).

Up to the 12-months-corrected-age visit, the investigator's assessment of an AE's relationship to study drug is part of the documentation process, but it is not a factor in determining what is or is not reported in the study. If there is any doubt as to whether a clinical observation is an AE, the event will be reported. Any SAE reported after the 12- and up to the 24-months-corrected-age visits must be assessed by the investigator regarding relationship to study drug and must if considered related (i.e. is a serious ADR) be reported in the study.

The severity and the relationship or association of the study drug in causing or contributing to the AE will be characterized as defined in [Sections 3.4.4.1.4](#) and [3.4.4.1.5](#).

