### **Serious Adverse Events**

Any AE considered serious by the investigator or subinvestigator or which meets SAE criteria ([Section 3.4.4.1.1](#)) occurring up to the 12-months-corrected-age visit, and any AE which meets SAE criteria ([Section 3.4.4.1.1](#)) and where a causal relationship between the event and the study drug is suspected by the investigator (serious ADR) occurring up to the 24-months-corrected-age visit, must be reported to PPD Pharmacovigilance (PVG) Department within 24 hours from the time study center personnel first learn about the event. The following contact information should be used for SAE and serious ADR reporting (Fax line for sending the SAE notification and the hotline and e-mail for questions):

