### **3.4.6 Health Economic Assessments**

#### **3.4.6.1 Health Care Utilization**

Information regarding health care utilization from the time of initial hospital discharge to home up to the 24-months-corrected-age visit will be collected through parent/primary caregiver reporting. The information will be collected as soon as informed consent has been provided (earliest at the 12-months-corrected-age visit), during telephone contacts at 15, 18 and 21 months corrected age and at the 24-months-corrected-age visit.

Parents/primary caregivers should be encouraged to use a notebook to keep track of all outpatient and inpatient visits and record information such as date, reason/diagnosis for visit, type of visit and duration of hospitalization. In case the caregiver is not able to provide information regarding health care utilization, the site will be asked to contact applicable health care providers for information. Approval from parents/primary caregivers to contact other health care providers will be collected as part of ICF procedure.

For outpatient care, the number of visits and type of health care provider will be recorded in the eCRF.

For inpatient care, the number of visits, reason/diagnosis for visit, number of days of hospitalization and number of days in the intensive care unit will be recorded in the eCRF.

The health care utilization information will not include standard preventive health care visits for children or vaccination programs.

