### 3.7.3 Safety Endpoints

The study has the following secondary safety endpoints to meet the objective “To compare the safety and tolerability of rhBSSL treatment in preterm infants with that of placebo treatment after oral administration in infant formula or PBM”:

- AEs up to 3 months and SAEs up to 12 months corrected age
- Bayley-III scores at 12 months corrected age
  - Cognitive domain composite score
  - Language domain composite score
  - Motor domain composite score

- Scaled scores for each subtest and for the cognitive domain (in total 5 scaled scores)
- Vomiting (frequency and volume)
- Vital signs (heart rate, blood pressure, body temperature)
- Levels of amylase, bilirubin, aminotransferases, sodium, and urea
- Levels of vitamins A and D
- Presence of rhBSSL antibodies

The study has the following secondary safety endpoints to meet the objective “To determine the long-term safety of rhBSSL treatment”:

- Serious ADRs up to 24 months corrected age

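### Between 12 and 24 months corrected age only serious events judged drug-related are reported, so all-cause deaths and SAEs have no planned comparison by arm and the long-term safety objective is weakly supported

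*Protocol*

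**What the plan says.** Up to the 12-months-corrected-age visit, reporting does not depend on cause. Section 3.4.4.1.2 states that "SAEs will be reported from the time the informed consent has been signed up to the 12-months-corrected-age visit". Section 3.4.4.1.3 adds that the investigator's causality assessment is documented, but "it is not a factor in determining what is or is not reported in the study".

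After that visit the rule changes. At the telephone contacts (15, 18 and 21 months) and at the 24-month visit, the legally acceptable representative "will be asked about any ongoing or previous (since last contact or visit) events that fulfills the SAE criteria" (Section 3.4.4.1.2). Then: "The investigator will then judge if a causal relationship between the SAE and the study drug is suspected". Section 3.4.4.1.3 says that an SAE from this period "must if considered related (i.e. is a serious ADR) be reported in the study". The 24-hour reporting rule uses the same filter: it covers events "where a causal relationship between the event and the study drug is suspected by the investigator (serious ADR) occurring up to the 24-months-corrected-age visit".

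The objectives in Section 2.1.2 include determining long-term safety. Section 3.7.3 gives that objective one endpoint: "Serious ADRs up to 24 months corrected age". Section 3.8.6 plans a separate analysis of serious ADRs to 24 months and limits SAE data to 12 months.

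Some information is collected to 24 months whatever its cause. On inpatient care, Section 3.4.6.1 asks for a count of admissions and adds: "reason/diagnosis for visit, number of days of hospitalization and number of days in the intensive care unit will be recorded in the eCRF". Section 3.4.6.3 records chronic conditions, and Sections 3.4.3.9 and 3.8.2 define and analyze a neurodevelopment disability composite.

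**The concern.** In a randomized, blinded trial, whether a late event is caused by treatment is best judged by comparing the arms. A related-only filter replaces that comparison with a case-by-case opinion, given after treatment has long ended and before the event is reported. Events judged unrelated never reach the safety data, so no SAP can restore them.

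Amendment 2.0 extended follow-up to 24 months partly to determine long-term safety. If few events pass the filter, the resulting table will be short in both arms and will say little about whether deaths or serious illness differed between them. The events have already been asked about, so the loss is avoidable.

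**Working it through.** The protocol states no figure for this point, so the check is mainly a comparison of its sections.

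**1. Elicited against reported**

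| Period | Elicited | Reported as safety data | Planned safety table |
|---|---|---|---|
| Consent to 12 months corrected age | All SAEs | All SAEs | SAEs including death (Sections 3.8.6, 3.8.6.1) |
| 12 to 24 months corrected age | All events meeting SAE criteria | Only those judged related | Serious ADRs only (Sections 3.7.3, 3.8.6) |

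Section 3.4.4.1.1 counts death and inpatient hospitalization as SAE criteria, so both fall under the filter in the second row.

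**2. Distance from treatment.** Treatment ends at Day 29 (Section 3.6.2). Table 6–2 places the 12-month visit after Day 415, ±14 days. The window therefore opens about 415 − 29 = 386 days after treatment ends, or 386 − 14 = 372 days at the early edge of the visit window. Section 3.4.4.1.5 treats an implausible temporal sequence as a reason to grade an event unlikely, and unlikely is counted as unrelated.

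**3. What other data could show a death or serious event**
- Inpatient visits with reason, hospital days and ICU days: recorded, but reported by caregivers, summarized descriptively as health economic endpoints (Section 3.8.3), and not among the items listed for MedDRA coding in Section 4.10. A death outside hospital produces no admission.
- Chronic diagnoses: recorded at 24 months and MedDRA-coded.
- Disability composite: analyzed by arm, but death is not a component (Section 3.4.3.9).
- Reason for withdrawal: recorded (Section 3.3.2), but death is not mentioned there.

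A death judged unrelated is thus assured of a place in none of the planned tables.

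**4. Internal consistency.** Section 3.4.4.1.2 opens by making the investigator responsible for reporting all AEs during the study whatever their relationship to study drug. Section 3.4.4.1.3 says all SAEs, again whatever the relationship, will be followed. Neither statement is reconciled with the related-only rule after 12 months.

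**5. What an empty serious ADR table would establish.** With zero events in n infants, the one-sided 95% upper limit is 1 − 0.05^(1/n).
- n = 432/2 = 216: 1.4%.
- n = 0.85 × 216 ≈ 184, using the 15% withdrawal anticipated in Section 3.8.1: 1.6%.

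Refused consent to the extension would widen this further. The limit applies to events attributed to study drug and does not bound all-cause deaths or SAEs.

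**6. Illustration of the filter (assumed rates).** Power = Φ{[|p₁ − p₂| − 1.96√(2p̄(1 − p̄)/n)] / √([p₁(1 − p₁) + p₂(1 − p₂)]/n)}, with n = 216 per arm and assumed 12-to-24-month SAE risks. For 10% against 20%: [0.10 − 1.96 × 0.0344]/0.0340 = 0.96, so power is 83%.

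| Assumed risks | All SAEs counted | 10% judged related | 5% | 2% |
|---|---|---|---|---|
| 5% vs 10% | 51% | 9% | 6% | 5% |
| 10% vs 20% | 83% | 13% | 9% | 6% |
| 15% vs 25% | 74% | 11% | 8% | 5% |

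With 184 per arm, the all-SAE column becomes 44%, 77% and 67%. The approximation is rough where events are few: 10% against 20% with 2% judged related gives about 0.4 and 0.9 expected events. The table shows how little the planned endpoint could detect under these assumptions. It does not measure data lost, because many SAEs would be admissions that are recorded anyway.

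**The case against.** A reader might infer that serious events in this window cannot be compared by arm at all, or that the long-term safety objective cannot be met. The protocol does not support either reading. Admissions with diagnosis, hospital days, ICU days and chronic diagnoses are recorded regardless of cause and can be summarized by arm. The disability composite has a by-arm odds ratio. The objective has a defined endpoint and analysis. Caregiver reporting and extension consent are no special weakness of the admissions data, since the SAE questions after 12 months depend on the same informants and the same consent.

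The restriction also looks deliberate. All-cause SAE reporting already runs for about a year after a 28-day treatment that Section 1.4 describes as most likely not absorbed. The filter appears consistently in Sections 3.4.4.1.2, 3.4.4.1.3, 3.7.3 and 3.8.6. The threshold is not high, because Section 3.4.4.1.5 counts possible as related. Site staff remain blinded (Section 3.6.7.2), so the judgment does not in itself favour an arm. How often investigators will call an event unrelated is not known.

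All of this stands, and it limits the point. It does not answer the remaining gap: deaths, serious events without admission, and any planned all-cause safety table by arm.

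**Conclusion.** The concern holds in limited form. From 12 to 24 months corrected age the protocol elicits all serious events but reports only those judged related, and it plans no comparison by arm of all-cause deaths or SAEs. The long-term safety objective is weakly supported. What is lost is deaths judged unrelated, unrelated serious events that lead to no admission, and a planned safety tabulation of the rest.

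That loss cannot be counted from the protocol, which gives no event rates or attribution rates. The zero-event limits of 1.4% to 1.6% concern attributed events only, and the power figures rest on assumed risks and assumed shares judged related. The finding itself depends on neither. Because the change is cheap, it is worth making.

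**What to change.** - In Sections 3.4.4.1.2 and 3.4.4.1.3, and in the matching footnotes to Table 6–2, require every death and SAE already elicited up to the 24-month visit to be entered in the eCRF, with causality as an attribute rather than a condition for entry.
- In Section 3.7.3, add all-cause deaths and SAEs to 24 months as an endpoint for the long-term safety objective, keeping serious ADRs as a subset.
- In Section 3.8.6, plan their tabulation by arm, alongside the inpatient admissions and diagnoses from Section 3.4.6.1.
- Reconcile the statements in Sections 3.4.4.1.2 and 3.4.4.1.3 that apply whatever the relationship to study drug with the rule for the period after 12 months.
- Expedited reporting after 12 months can stay limited to serious ADRs.

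The cost is protocol wording plus modest site data entry and coding for events already asked about. The extension consent described in Sections 3.4 and 4.3 names serious ADRs, so its wording should be checked at the same time.
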